### Sample size

This study is powered to detect a change according to cluster in admissions and in-hospital mortality per 100 STEMI cases. A sample size of 1581 participants will provide 80% power to detect an estimated 15% reduction or greater in mortality from the estimated baseline of 3.18 per 100 STEMI cases, with an alpha of 0.05, intra-cluster correlation of 0.005, and 20% non-response rate. The effect size is a conservative estimate based on past pilot experience (ClinicalTrials.gov, NCT04014972).

Data will be collected via the China CPC Data Reporting Platform (http://data.chinacpc.org/). Registered hospitals are instructed to enroll consecutive patients admitted to hospitals with acute cardiac events, and real-time reporting, as required. To be eligible, we will collect data from patients who meet the following criteria: (1) age 18 years or older; (2) a discharge diagnosis of STEMI based on ischemic symptoms, ECG changes, or positive cardiac markers; (3) admitted via all kinds of modes including directly by self, via EMS, transferred in, or in-hospital.

### Project activities

Taking advantage of ongoing monitoring and evaluation of the quality of STEMI care and continuous data collection in the CHANGE program, this study will achieve the goals and objectives through the following tasks and approaches.
Task 1. Design of optimized QI initiatives

Specific activities
Summarize China’s current experience in improving the quality of STEMI care in response to COVID-19 and focusing on the selected cities.Identify priority intervention areas in the quality of the care response to COVID-19.Identify key players and actors and their roles in optimizing QI initiatives in China.Develop hospital-based interventions based on the current QI initiatives.

Approaches
Case studies

We will carry out case studies in the three selected cities, and we will summarize practices in implementation of the current QI initiatives, analyze the development of health care systems and infection-control measures, and assess the demographic profile of the population and utilization of emergency and medical services.
2)Qualitative interviews and formative research

This study will draw upon a series of interviews (face-to-face and by telephone and email) and focus group discussions conducted with key informants from governmental and nongovernmental agencies, organizations, and institutions. The interviews and discussions will be based on the initial outputs produced in the pilot study and case studies. A list of questions will then be developed and submitted to the study organization for consultation, review, comments, and further clarification.
(2)Task 2. Implementation and evaluation of optimized QI initiatives

Specific activities
Implement the optimized QI initiatives in the 24 selected hospitals in a staggered manner.Compare longitudinal changes in the quality metrics of STEMI care and assess the clinical effectiveness of the optimized QI initiatives.Analyze changes in the measures of reach, adoption, implementation, and maintenance, to evaluate the implementation strategy of the optimized QI initiatives.Identify barriers and facilitators contributing to implementation of the optimized QI initiatives.

Approaches
Stepped wedge cluster randomized control trial

This pragmatic design leverages the staggered rollout of the optimized QI initiatives and will facilitate the assessment of effectiveness and implementation strategy. The trial will include four clusters in which the optimized QI initiatives are implemented sequentially every 3 months. A local project office in each district will be set up to manage the process of implementation. The optimized QI initiatives will be sequentially implemented by cluster [28, 29], and baseline assessment will be conducted within 3 months prior to implementing the optimized QI initiatives (Table 3).
2)Evaluation of the optimized QI initiatives

**Table 3 Tab3:**
[figure not shown]
Optimized quality improvement (QI) initiatives, timeline, and data collection based on staggered implementation

The black portion in rows indicates the intervention phase and the gray portion indicates the control phase

To evaluate the effectiveness and implementation of the optimized QI initiatives, we will conduct a pragmatic hybrid type II effectiveness-implementation study, as this allows for simultaneous mixed-methods evaluation. All measures will be organized using a modified RE-AIM framework. Table 4 summarizes outcomes, data collection, and analysis plans organized by objective and adapted RE-AIM domains.

**Table 4 Tab4:** Outcomes, data collection, and analysis plans organized by adapted RE-AIM domains

Outcomes	Indicators	Data source	Indicator definition
Service outcome	Number of admissions	Hospital-based assessments	The number of admissions for STEMI patients
	PCI rate	Hospital-based assessments	The proportion of STEMI patients who receive PCI
	Percentage of EMS transfer	Hospital-based assessments	The percentage of STEMI patients who are transferred by EMS agency
	Onset-to-FMC time	Hospital-based assessments	The time from onset to first medical contact of STEMI patients
	Door-to-balloon time	Hospital-based assessments	The time from arrival in hospital to PCI of STEMI patients
	FMC-to-device time	Hospital-based assessments	The time from first medical contact to PCI of STEMI patients
	Percentage of onset-to-FMC time ≤ 60 min	Hospital-based assessments	Percentage of STEMI patients with the time from onset to first medical contact ≤ 60 min
	Percentage of Call-to-EMS time ≤ 15 min	Hospital-based assessments	Percentage of STEMI patients with the time from calling EMS agency to ambulance arrival ≤ 15 min
	Percentage of Door-to-balloon time ≤ 60 min	Hospital-based assessments	Percentage of STEMI patients with the time from arrival in the hospital to PCI ≤ 60 min
	Percentage of FMC-to-device time ≤ 90 min	Hospital-based assessments	Percentage of STEMI patients with the time from first medical contact to PCI ≤90 min
Patient outcome	In-hospital mortality	Hospital-based assessments	Proportion of STEMI patients discharged death
	1-year mortality	Community-based household survey by telephone	Death rate of the STEMI patients within 1 year after hospitalization
	1-year complication rate	Community-based household survey by telephone	Incidence rate of new vascular events of STEMI patients within 1 year after hospitalization
Implementation outcome—reach	Number of patients visits	Community-based household survey	Proportion of the STEMI patients reporting care at a health facility
	Number of residents receiving health education	Community-based household survey	Number of individuals who receive education on STEMI awareness and COVID-19 knowledge
	Training the QI initiatives for Health providers	Questionnaire survey on healthcare providers	Number and proportion of the healthcare providers who receive the QI initiatives training
Implementation outcome —adoption	Community engagement	Community-based household survey	Number of community residents attending the optimized QI initiatives
	Health providers engagement	Questionnaire survey on healthcare providers	Number of health providers attending the optimized QI initiatives
	Behavior change of healthcare providers	Questionnaire survey on healthcare providers	Change score of healthcare providers in compliance with protocol of clinical guidelines
	Health literacy change of residents	Community-based household survey	Change score of health literacy related to STEMI awareness and COVID-19 knowledge of individuals
	Attitude of health facility directors	Key informant interviews	Degree of acceptance of the optimized QI initiatives by directors from hospitals and EMS agency
Implementation outcome—implementation	Fidelity	Key informant interviews	Degree that the optimized QI initiatives are implemented as planned in original protocol
	Feasibility	Key informant interviews	Extent that the optimized QI initiatives can be carried out in a specific setting
	Outer context	Key informant interviews	Macro-level external factors including social, funding, and leadership
	Inner context	Key informant interviews	Micro-level internal factors including NHC partnership, the programmatic staff, feedback, hospitals, EMS agency, community, household, and individual level
Implementation outcome —maintenance	Sustainable of the effectiveness	Key informant interviews	Views on maintaining effectiveness from policy makers, health facility directors, healthcare providers, and residents
	Satisfactory of stakeholders	Key informant interviews	Satisfactory on effectiveness and implementation strategy of the optimized QI initiatives of policy makers, health facility directors, healthcare providers, and residents
	Financial sustainable	Key informant interviews	Views on funding and return on investment from policy makers and health facility directors
	Institutionalization of interventions	Key informant interviews	Core components which are transferrable and where local adaptation is needed for replication in other settings

*RE-AIM* Reach, effectiveness, adoption, implementation, maintenance; *PCI* Percutaneous coronary intervention; *STEMI* ST segment elevation myocardial infarction; *EMS* Emergency medical services; *FMC* First medical contact; *QI* Quality improvement; *COVID-19* Coronavirus disease 2019; *NHC* National Health Commission

To measure outcomes, four components of the proposed work at each cluster will be conducted: i) hospital-based assessments, ii) questionnaire surveys of health care providers, iii) community-based household surveys, and iv) key informant interviews. Further details about each study component are described below, with Table 3 summarizing the timeline.
i.Hospital-based assessments

The assessments will be carried out at hospital level by collecting data via the China CPC Data Reporting Platform. Data elements for quality-of-care metrics will be selected based on the ACC/AHA clinical data standards. The assessments will be conducted in each cluster at baseline, at the start of the trial, and at subsequent 3-month intervals until the end of the trial.
ii.Questionnaire surveys of health care providers

Health care providers’ experiences and perceptions will be assessed via questionnaire surveys, to inform the consideration of reach and adoption efforts. Questionnaire survey data will be collected from dedicated regional coordinators, cardiologists, medical staff in emergency departments, and hospital managers. The assessments will be conducted in each cluster at baseline, at the start of the trial, and at subsequent 6-month intervals until the trial ends.
iii.Community-based household surveys

Household surveys will be conducted at the community level using a self-designed questionnaire to inform consideration regarding patient outcomes, as well as reach and adoption efforts. Surveys will target patients with STEMI and the general catchment population. The surveys will be conducted in each cluster at baseline, at the start of the trial, and at subsequent 6-month intervals until the trial ends.
iv.Key informant interviews

Qualitative interviews will be completed with key informants to assess adoption and maintenance. Key informants will include implementing partners in the program and local governments, as well as clinical and administrative employees in hospitals and EMS agencies. The key informant interviews will be conducted in each cluster at baseline, at the start of the trial, and at subsequent 6-month intervals until trial ends.
(3)Task 3. Development of scale-up activities in the optimized QI initiatives

Specific activities
Identify barriers and facilitators to program implementation fidelity and feasibility while also documenting contextual factors.Investigate core requirements for implementing the optimized QI initiatives in response to COVID-19.Identify gaps between the current experience in China’s practices of implementing the optimized QI initiatives.Develop strategic and policy options for scale-up activities of the optimized QI initiatives under two scenarios, including the outbreak stage of a major public health emergency and the pandemic period.

Approaches
Stakeholder-based participatory research

Stakeholder-based participatory research will be conducted at the end of the stepped wedge cluster randomized control trial, to focus on partnerships, engagement, co-learning, and building on existing assets within China. Major stakeholder agencies and organizations will be invited to participate in this exercise. The exercise will help to identify factors influencing the implementation strategy using the CFIR framework, investigate core requirements for implementing the optimized QI initiatives in response to COVID-19, and identify gaps between the current experience in China’s practices in implementing the optimized QI initiatives according to the designed interview outline.
2)Policy dialogue and round-table discussion

We will translate the findings and results of this study into policy briefs and reports. Both electronic and paper-based briefs and internal policy analytic reports will be distributed through university think tank-based and extra-university channels to relevant decision-making bodies and agencies. A round-table discussion will be convened, to allow for feedback and comments on the results and findings of the study and provide opportunities for knowledge uptake among all stakeholders, decision makers, and executive entities, using push techniques to elicit pull by tailoring dissemination, to address the needs and concerns of decision makers.

### Statistical methods

Task 1. Design of the optimized QI initiatives

For Task 1, the analytic hierarchy process will be applied to identify the priority intervention areas in the quality-of-care response to COVID-19. A facilitated and structured interview matrix technique will be used to analyze the interview results for organizational analysis and strategic planning of priority settings. The structured interview matrix will follow a graded approach to collaboration involving discussion at three levels, using a three-step process: (1) interviews conducted by participants in the group; (2) small group deliberation; and (3) a facilitated, plenary discussion with the full group.
(2)Task 2. Implementation and evaluation of the optimized QI initiatives(3)To investigate the effectiveness of the optimized QI initiatives with respect to quality metrics of STEMI care in response to COVID-19

Primary analysis will be performed according to the intention-to-treat principle. All analyses of outcomes will be at the individual level but will account for the clustering of patients at the hospital level. Comparisons of quality metrics between intervention and control participants will be conducted using the *t*-test and *χ*^2^ test. To analyze intervention effects, generalized estimating equation models will be used to account for the clustering within hospitals. The primary model will include a fixed effect for time and a binary variable for the effect of the intervention. The intervention effects will be summarized as the resulting odds ratios and difference of proportions for binary outcomes or mean differences for continuous outcomes. We will also conduct two-level generalized linear mixed models with patient and hospital as the first and second levels, respectively, using covariate-adjusted analyses. The model will also include the severity of the COVID-19 pandemic as a confounding factor. Appendix Table 2 depicts how the results will be displayed.
2)To examine the implementation strategy of the optimized QI initiatives using measures of reach, adoption, implementation, and maintenance in response to COVID-19

We will use a mixed-effects generalized linear model to compare pre-intervention to post-intervention proportions for each metric of reach and adoption, while adjusting for clustering at the hospital level and time and allowing for hospital-level estimates to be random effects; Appendix Table 3 shows how the results will be displayed. Evaluation of implementation and maintenance will be completed using questionnaires and interviews following the CFIR framework. The results of CFIR domains will complement quantitative data collected to evaluate implementation strategy and will assess emerging themes in identifying barriers and facilitators contributing to implementation of the optimized QI initiatives, to minimize adverse impacts of COVID-19 outbreak (Appendix Table 2).
(3)Task 3. Development of scale-up activities of the optimized QI initiatives

For task 3, the CFIR framework will be used to identify factors that may emerge in various contexts and that influence intervention implementation and effectiveness. We will use a template-analysis approach to code and organize our data for analysis by CFIR domain, including intervention characteristics, inner setting, outer setting, characteristics of individuals involved in implementation, and implementation process. Then, we will populate analytic matrices with the information for cross-case analysis of patterns in barriers and facilitators related to each of the program components. Our analytic matrices will facilitate simultaneous viewing of a large volume of data, to make between-practice comparisons and identify similarities, differences, and trends in how practices have experienced implementation.

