*QI* Quality improvement; *CHANGE* National Chest Pain Center Accreditation Program; *CPC* Chest pain center; *EMS* Emergency medical services; *ACC/AHA* American College of Cardiology/American Heart Association; *COVID-19* Coronavirus disease 2019; *STEMI* ST segment elevation myocardial infarction

Sampling

In this study, we will conduct a rollout to registered hospitals every 3 months, which will be based on the pilot experience, local contextual factors, budgetary and feasibility considerations. Patients with STEMI in registered hospitals will be consecutively enrolled in five 3-month steps. No intervention will be applied in the first step among all registered hospitals. Hospitals will be randomly allocated to one of four clusters, with six hospitals in each cluster. Each cluster will commence the intervention at one of the four remaining steps. All hospitals will be on the intervention in the final step. Characteristics of hospitals with STEMI cases enrolled during January and June 2020 are shown in Table 2, by district (Table 2).

**Table 2 Tab2:** Characteristics of sample hospitals, by district

City	District	Population	Land area (km^2^)	Number of hospitals	STEMI patients	In-hospital mortality
Wuhan	Jianghan	496,289	28.3	3	459	1.53
	Qiaoko	528,604	40.1	4	319	3.13
Suzhou	Gusu	957,500	83.4	4	167	3.86
	Kunshan	1,665,900	931.5	6	157	1.27
Shenzhen	Futian	1,633,700	78.5	4	250	6.00
	Luohu	1,039,900	78.7	3	229	4.37

*STEMI* ST segment elevation myocardial infarction

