### Pilot study

We have performed a retrospective cohort study drawing on unified registered-hospital report data from the CHANGE program. We investigated the effectiveness of the current QI initiatives in terms of quality metrics of STEMI care during January 2020 and June 2020 by comparing the data at baseline and in the final quarter. We then compared changes in the quality metrics of STEMI care between January and June 2019 and between January and June 2020 using difference-in-difference analysis.

The primary results of the polit study are as follows. First, baseline and quarterly data during January 2016 and June 2019 demonstrated that implementing the current QI initiatives significantly improved many process indicators. For example, the onset-to-device time decreased from 291 minutes to 233 minutes, and the percentage of cases with FMC-to-device time≤ 90 minutes increased from 43.0% to 54.1% between baseline and the final quarter. Second, during January and July 2020, admissions of patients with STEMI decreased by 42%, compared with the same period in 2019. Baseline and quarterly data showed that door-to-balloon and the FMC-to-device median (q1, q3) time increased from 17.5 (10.0, 46.0) and 52.0 (12.0, 86.0) minutes to 34.0 (15.0, 48.0) and 63.0 (15.0, 94.0) minutes, respectively (*p* = 0.001, *p* = 0.005). The onset-to-FMC time accounted for more than 70% of the total delayed time. Third, compared with January to June 2019, many process indicators deteriorated from January to June 2020. For example, the proportion of patients admitted via EMS was only 4.2% in 2020, much lower than that in 2019 (9.3%, *p* = 0.013), and rate of PCI practice declined from 71.3% to 60.1% (*p* = 0.002).

The additional expected primary results of the pilot study will include the following: First, the CFIR framework will be developed to support evaluation of implementation of the current QI initiatives within the context of COVID-19, and to produce actionable evaluation findings intended to improve implementation in a timely manner; Second, In-depth interviews with key informants will be conducted to identify barriers and facilitators to implementation of the current QI initiatives that may emerge in the context of COVID-19, using the CFIR framework to guide data collection, coding, analysis, and reporting of actionable findings for the design of the optimized QI initiatives.

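### The unadjusted t-tests and chi-square tests of outcomes between intervention and control patients are confounded with calendar time and conflict with the plan's own clustering rule; the primary model is not affected

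*Protocol article*

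**What the plan says.** The relevant text is the Task 2 effectiveness paragraph of Statistical methods. Its general rule is: "All analyses of outcomes will be at the individual level but will account for the clustering of patients at the hospital level". The next sentence reads "Comparisons of quality metrics between intervention and control participants will be conducted using the" t-test and chi-square test. It mentions no step, period, stratum or cluster correction.

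The paragraph then turns to effect estimation: "To analyze intervention effects, generalized estimating equation models will be used to account for the clustering within hospitals". It continues: "The primary model will include a fixed effect for time and a binary variable for the effect of the intervention". Odds ratios, differences of proportions and mean differences are the summaries of the intervention effect. Covariate-adjusted two-level mixed models are added, followed by: "The model will also include the severity of the COVID-19 pandemic as a confounding factor".

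The Intervention section (under Sampling) fixes the design. "Patients with STEMI in registered hospitals will be consecutively enrolled in five 3-month steps", and "No intervention will be applied in the first step among all registered hospitals". Four groups of six hospitals cross over one per step, and all 24 hospitals are on the intervention in the fifth step.

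The quality metrics are outcomes, not baseline characteristics. Task 2 under Project activities pairs changes in them with the assessment of clinical effectiveness, and Table 4 lists PCI rate, EMS transfer and treatment times as service outcomes.

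**The concern.** In a stepped wedge, patients treated under intervention and under control are not contemporaneous randomised groups. The first step is all control and the last is all intervention, so a comparison of the two sets across the trial compares later patients with earlier ones. Any change over time that would have happened anyway is counted as a difference between conditions.

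That matters here because the document's own figures move a great deal with the pandemic. The Pilot study section reports that the "rate of PCI practice declined from 71.3% to 60.1" per cent between the first halves of 2019 and 2020, and that EMS admission fell from 9.3% to 4.2%. The Strengths and limitations section lists temporal trends as a threat to validity and relies on the analysis plan to mitigate it.

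The second fault is internal. Plain t-tests and chi-square tests treat patients as independent, so they do not satisfy the clustering rule in the sentence just before them.

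At stake is a second set of p-values for the intervention-control comparison, with nothing to say that it is descriptive or which set prevails if the two disagree.

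**Working it through.** The protocol gives no figure of its own for this comparison, so there is none to reproduce.

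**Inputs.** From the Intervention section: 24 hospitals, five 3-month steps, six hospitals crossing over at each of steps 2 to 5. From Sample size: 1,581 patients, alpha 0.05 and intra-cluster correlation (ICC) 0.005. The 1,581 is taken as stated; whether it is adequate is a separate question on which this point does not depend. From Pilot study: PCI rates of 60.1% and 71.3%. Assumptions: equal numbers of patients per hospital and step, two-sided tests, no intervention effect, and a linear return from 60.1% to 71.3% across the five steps.

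**1. Time imbalance.**

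| Step | 1 | 2 | 3 | 4 | 5 |
|---|---|---|---|---|---|
| Control hospital-periods | 24 | 18 | 12 | 6 | 0 |
| Intervention hospital-periods | 0 | 6 | 12 | 18 | 24 |

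- Mean step, control: (24×1 + 18×2 + 12×3 + 6×4)/60 = 120/60 = 2.0.
- Mean step, intervention: (6×2 + 12×3 + 18×4 + 24×5)/60 = 240/60 = 4.0.
- The gap is 2 steps, or six months. The whole trend spans 4 intervals, so a linear trend puts 2/4 = half of its total change into the contrast.

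**2. Spurious difference, full recovery.** Rates by step are 60.1, 62.9, 65.7, 68.5 and 71.3%.

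- Control: 0.4×60.1 + 0.3×62.9 + 0.2×65.7 + 0.1×68.5 = 62.9%.
- Intervention: 0.1×62.9 + 0.2×65.7 + 0.3×68.5 + 0.4×71.3 = 68.5%.
- Difference: +5.6 points, which is half of 11.2.

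**3. How often it would be significant at 1,581 patients (790.5 per condition).** The standard error (SE) is √[2p(1−p)/790.5], with p the mean of the two rates.

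- Full recovery: p = 0.657, SE = 0.0239, z = 0.056/0.0239 = 2.34. Rejection probability ≈ Φ(2.345 − 1.96) = 65%.
- Half recovery (61.5% against 64.3%): p = 0.629, SE = 0.0243, z = 0.028/0.0243 = 1.15. Rejection probability ≈ Φ(1.15 − 1.96) = 21%.

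**4. Sensitivity to the number of patients.** The six-month total in Table 2 is 459 + 319 + 167 + 157 + 250 + 229 = 1,581. If that rate held for 15 months, the trial would see 1,581 × 15/6 ≈ 3,950 patients. With 1,976 per condition, SE = 0.0151 and z = 3.71, so rejection is about 96% for the full recovery, and about 45% for half of it. The 3,950 is an extrapolation, not a planned number.

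**5. Simulation, 13 patients per hospital and step, no intervention effect.** The chi-square results are from 1,000 runs each.

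| Scenario | ICC | Chi-square rejects |
|---|---|---|
| No trend | 0.005 (stated) | 4.9% |
| No trend | 0.05 (assumed) | 11.6% |
| PCI 60.1% to 71.3% | 0 | 66.1% |
| PCI 60.1% to 71.3% | 0.005 | 65.3% |
| PCI 60.1% to 71.3% | 0.05 | 61.0% |
| Mortality 4.13% to 2.23% (assumed: 3.18% × 1.3 to × 0.7) | 0.005 | 19.3% |

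The exchangeable logistic GEE, with a fixed effect for each step and bias-reduced standard errors, rejected in 4.5% of 200 runs under the full PCI recovery at ICC 0.005. The Monte Carlo standard error is √(0.05×0.95/200) = 1.5 points, so this agrees with the nominal 5%.

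**The case against.** The strongest reply is that these tests do not decide anything. The same paragraph assigns intervention effects to the GEE with a fixed time effect and hospital clustering, takes the reported effects from that model, and adds mixed models and pandemic severity. The t-tests and chi-square tests are not called primary, and they may have been meant only for a descriptive table. The appendix table that shows how results are displayed is not at hand. That stands, and it limits the point to a companion analysis.

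It can also be said that the text does not state that the tests run across all steps. This is true; pooling is a reading. But no restriction to a step is given, and the comparison is worded as intervention against control participants. Tests within each of steps 2 to 4 would remove the time confounding, though not the conflict with the clustering rule.

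Finally, the trend is hypothetical. The two PCI rates compare the first halves of 2019 and 2020, while the trial was registered in February 2021. Nothing shows that PCI use was still at 60.1% in step 1 or would recover in a straight line. That also stands, and it is why the size is given as a range. The direction could reverse as well: if care worsened over the trial, the same tests could hide a benefit or suggest harm.

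The reply does not rescue the sentence itself. It states a method for comparing outcomes that ignores time and conflicts with the sentence before it.

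**Conclusion.** The point holds for the unadjusted tests, at moderate severity. Time confounding is the main fault, and it follows from the design: half of any linear secular change enters the contrast. For PCI use at 1,581 patients, the chance of a spurious significant result is about 65% with a full linear recovery and about 21% with half of it. For mortality it is about 19% under the assumed trend. All these figures rest on no intervention effect, equal patient numbers per hospital and step, and tests run across all steps.

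The conflict with the clustering rule is plain on the page, but its numerical effect is negligible at the stated ICC of 0.005. It would matter only at clearly larger values.

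A reader might infer that the trial would declare pandemic recovery to be an intervention effect. The protocol does not support that. Its primary model carries a fixed time effect and hospital clustering, and it held its error rate in the check above. What remains is a set of companion p-values that could mislead beside a sound primary analysis.

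**What to change.** Delete the sentence on t-tests and chi-square tests of outcomes, or replace it with a descriptive display of each outcome by step and allocation, without p-values. State that every effect estimate, confidence interval and p-value comes from the time-adjusted, hospital-clustered model. The cost is one sentence in Statistical methods, with no change to data collection, sample size or patient burden.
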